### Definition of adverse events and defects

Adverse Event" means any undesirable or unintended illness or disorder and its symptoms (including abnormal laboratory values) that occur in a subject, user, or other person (hereinafter referred to as “Subject,” (2) The term "Unintended Diseases" shall include all undesirable or unintended diseases or disorders and their signs (including abnormalities in clinical laboratory test values) that occur in subjects and other persons (hereinafter referred to as “Subjects”. However, the occurrence of such symptoms in a person other than the subject shall be limited to those suspected to be caused by the use of the investigational device.

Failure means any failure of the investigational device in terms of quality, safety, performance, etc., including breakage or malfunction, whether due to design, delivery, storage, or use.

(2) In the event of an adverse event or failure of the investigational device or subjects, the investigator shall immediately take appropriate measures to ensure the safety of the subjects and to report the event. The results shall be recorded in the Case Report Form.

### Duration, frequency, and methods to examine adverse events/defects and serious adverse events/defects

The investigator or medical institution personnel are responsible for detecting, recording, and reporting adverse events or events that meet the definition of a serious adverse event.

Adverse events should be collected from the time of obtaining consent to the time of follow-up or discontinuation of the study. The collection period for failure is from the time of use of the investigational device.

1) Adverse events

The investigator shall record the following items regarding the adverse events that occur:

- Causal relationship with noisy GVS (no causal relationship with noisy GVS, a causal relationship with noisy GVS cannot be ruled out)
- Time (date (hour)* of onset, date of conversion, or date of confirmation of conversion)
- *: Time will be recorded only for adverse events during the use of the investigational device.
- Severity (severe, moderate, mild)
- Mild: Adverse events that are easily tolerated, cause only slight discomfort, and do not interfere with daily life
- Moderate: Unpleasant adverse event that interferes with the daily life
- Severe: Adverse event that prevents the patient from leading a normal daily life
- Severity (severe, non-serious)
- Status of Noisy GVS discontinuation
- Treatment
- Outcome of an adverse event (recovered, mildly recovered, not recovered, with sequelae, died, unknown)

2) Defect

When a defect occurs, the investigator (or subinvestigator) shall record the following items related to the defect

- Status of the risk of a health hazard
- Details of the defect
- Date and time of onset
- Severity of incident
- Predictability

### Definition of serious adverse events

Serious adverse events are defined as any of the following among adverse events

(1) Event resulting in death

(2) Life threatening event

(3) Event requiring hospitalization or extended hospitalization for treatment

(4) Permanent or significant disability or disorder

(5) Event resulting in the detection of congenital anomalies

(6) Other serious medical events

Other situations, i.e., events that are not immediately life-threatening or result in death or hospitalization, but are serious enough to put the subject at risk or require treatment to avoid the consequences described above, should also be considered as serious.

### Response to serious adverse events and defects

If a serious adverse event or a defect with the potential to cause a serious adverse event (hereinafter referred to as "defect etc.") occurs during the clinical trial period, the coordinating investigator shall handle the information on the relevant defect, in accordance with the "Procedures for Handling Safety Information".

The coordinating investigator shall make a decision on whether or not to report to the Minister of Health, Labour, and Welfare (the "Authority") in accordance with the "Procedures for Handling Safety Information".

If it is judged that a report to the authority is necessary, the investigator who conducts the clinical trial on his/her own shall prepare a report to the authority and submit it to the Pharmaceuticals and Medical Devices Agency (PMDA) within the reporting deadline in Table 4.

The coordinating investigator shall share the information with investigators and the investigational device provider at each medical institution in accordance with the "Procedures for Handling Safety Information".

Table 6. Serious adverse event reporting deadlines

|  | Unforeseen events | Foreseen events |
| --- | --- | --- |
| Event resulting in death  Event that is life-threatening | Seven days  Periodic report every year | Fifteen days  Periodic report every year |
| Event requiring hospitalization or extended hospitalization for treatment  Event resulting in permanent or significant disability or disorder  Event leading to detection of a congenital anomaly | Fifteen days  Periodic report every year | Periodic report every year |
| Defect that may lead to a serious adverse event | Thirty days  Periodic report every year | |

### Expected adverse effects

The adverse events reported in the clinical studies conducted to date were cerebral infarction, dizziness, and right-sided hearing loss. Of these, there were no adverse events (adverse effects) for which a causal relationship with the noisy GVS could not be ruled out. The event of equipment failure was "fast lighting of the power ON/BATT LED of the main body of the stimulator".

Anticipated Defects

- If the patient is very sensitive to electrical stimulation, the electrical stimulation may cause pain.
- If the vestibular nerve is very sensitive, symptoms, such as dizziness, nausea, headache, and the possibility of falling while standing or walking may occur.
- Individuals with allergies may develop hives or dermatitis to the surface electrode applied to the back of the ear.
- Failure of the electrical stimulator may result in interruption of the electrical stimulation or under- or over-current flow than the programmed value.
- If the power switch of the main body of the stimulator is turned from ON to OFF and back ON again in less than 3 s, the LED may blink fast and switch off the electrode, light up constantly, or become unlit, causing the output to stop.

# Data Analysis and Statistical Considerations

Details of the tabulation and analysis will be described in the "Statistical Analysis Protocol". Any changes from the analyses described in this study protocol will be described in the "Statistical Analysis Protocol," "Statistical Analysis Report," and "Summary Report".

If this clinical trial is terminated during the course of the study, all the available data will be listed and appropriate statistical analyses will be performed.

## Study design considerations

### Setting of the number of cases

The target number of patients for this clinical trial will be set at 60 (50 enrolled in the main study and 40 completed).

### Rationale for setting the number of cases

In a previous study^6)^, the total trajectory lengths of healthy subjects, patients with unilateral peripheral vestibular impairment, and patients with bilateral peripheral vestibular impairment were 1.69, 2.08, and 2.17 cm (per second), respectively. Since an improvement of approximately 19% in patients with unilateral peripheral vestibular disorder and 23% in patients with bilateral peripheral vestibular disorder would be consistent with normal subjects, we consider that clinical significance would exist if there is an improvement in the total trajectory length of at least 10%, equivalent to approximately half of the 19% and 23% improvement between the placebo period and the use of this experimental device.

The Type 1 error and detection power in 1000 simulations are shown in the table below, assuming the following [1] for the total trajectory length data, based on the investigator-initiated clinical trial data. The target number of patients is set to 60 (50 enrolled and 40 complete), assuming a dropout rate of 20% and a suboptimal intensity of 15%.

Table 7. Relationship between the number of cases and detection power (%)

| Effect of treatment^*1^ | N=30 | N=40 | N=50 |
| --- | --- | --- | --- |
| 0% ^*2^ | 4.7 | 5.2% | 4.7 |
| 5% | 31.5%. | 38.2% (in the case of the | 46.1% (in the case of the |
| 7% | 55.0 | 70.6% | 78.2 |
| **10%** | **84.1%** | **91.2%** | **96.1%** |

*1 Rate of improvement in the GVS period relative to the placebo period.

*2 Rows with 0% treatment effect represent Type 1 error. The nominal significance level of 5% was confirmed to be ensured.

[1] In the investigator-initiated clinical trial data, the greatest improvement occurred immediately after stimulation (23% in Session II and 19% in Session III), and improvement rates of more than 12% existed up to 3 h later (see the Table below). To be somewhat more conservative than the investigator-initiated clinical trial data, the standard deviation of the improvement rate of the total trajectory length in the GVS and placebo periods was set to 30% and the correlation coefficient of the improvement rate between each time point to 0.3. In addition, the simulated improvement rate data were generated from a multivariate truncated normal distribution cut in the range [-80, 80]. The magnitude of the treatment effect was assumed to be constant throughout the 3 h and varied from 0%, 5%, 7%, and 10%.

Table 8. Descriptive statistics for the percentage improvement in the total trajectory length in exploratory clinical studies as well as the correlation coefficient (%) between the rate of improvement immediately after stimulation and the rate of improvement at each time point

|  |  | Average | Standard deviation | Minimum value | Maximum value | Correlation coefficient |
| --- | --- | --- | --- | --- | --- | --- |
| Session II | |  |  |  |  |  |
|  | Immediately after stimulation | 23.1% | 14.7 | 3.1% | 49.0 | 1.00 |
|  | 30 min later | 17.1% | 14.1% | -14.3 | 44.3% | 0.49 |
|  | One h later | 16.5%. | 18.0%. | -21.1% | 52.3 | 0.53 |
|  | Two h later | 17.1% | 15.0%. | -6.3%. | 41.2 | 0.30 |
|  | Three h later | 14.8 | 11.1% | -0.9%. | 32.3 | 0.62 |
| Session III | |  |  |  |  |  |
|  | Immediately after stimulation | 19.2% | 23.6 | -25.2 | 69.5%. | 1.00 |
|  | 30 min later | 17.0%. | 22.7 | -22.5%. | 70.0 | 0.84 |
|  | One h later | 14.8 | 21.5%. | -13.1% | 70.1% | 0.74 |
|  | Two h later | 12.6%. | 25.5%. | -31.9%. | 61.3% | 0.70 |
|  | Three h later | 14.0% (1.0) | 26.3 | -43.5%. | 57.2 | 0.82 |

### Re-estimation of the number of subjects

A re-estimation of the number of subjects has not been planned for this study.

## Consideration of data analysis

### Completed case

A subject who has completed all stimuli and tests specified in the study protocol and has completed post-hoc (additional and follow-up) investigations is considered to have completed the study.

### Analysis sets

Full Analysis Set (FAS) for efficacy

Of the enrolled patients in the study, the full analysis set will consist of patients who visited the hospital in either Session I or Session II, were fitted with the investigational device, and had at least one efficacy endpoint measured. However, the following patients will be excluded:

- GCP non-compliance: Patients who have not given appropriate informed consent

Per Protocol Set (PPS)

From the FAS, the following subjects will be excluded from the PPS.

- Subjects not meeting the selection criteria
- Subjects that violated the inclusion and exclusion criteria
- Subjects who administered concomitant prohibition therapy
- Subjects who did not visit the sites in both Session I and Session II
- Other subjects with serious protocol deviations

Safety Analysis Set (SAS)

Of the enrolled patients, the SAS shall consist of those patients in whom at least one safety endpoint was evaluated.

If a subject is excluded from the analysis, the details and reasons should be described in the Clinical Study Report.

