## Enrollment Procedure

All subjects whose written consent has been obtained and who have been screened and found eligible will be enrolled into the study. A central registration system using subject identification codes will be used, and all subject enrollments will be done on the internet. Provisional and full enrollment will be conducted for this study.

1. Provisional enrollment

All the subjects from whom written consent is obtained and who are screened and found eligible will be provisionally enrolled.

1. Full enrollment

Only subjects with optimal intensity will be enrolled in the study. Subjects with suboptimal intensity will be stopped at this point, and the study will be terminated after confirming safety 2 weeks later.

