**Optimal intensity consideration:**

To determine this optimal intensity, stabilometry is performed. In multiple continuous current intensities, the total trajectory length is shortened to below the sub-threshold sensitivity (the minimum current intensity where the noisy GVS-specific stimulus (shortly spaced continuous stimuli) is felt). A patient who shows an improvement of at least 10% in the current intensity with the best improved trajectory length among those multiple continuous current intensities when compared with the total trajectory at baseline (the average of three measurements during closed-eye standing with no current) was defined as a patient with existing optimal intensity and the ‘enrolment of the patient in this study’ is performed.

The optimal intensity is defined as the current that improves the total trajectory length the most among the above multiple currents.

Procedures for examining the optimal intensity

1) The subject stands with closed eyes with no foam rubber placed (without interrupting somatosensory input) and no electric current applied to the stabilometer, and after the body sway reaches a steady state, the gravimetric sway is measured for 30 s.

2) Perform the measurement 1) three times with an interval of 2 min.

3) After the measurement, after an interval of 2 min of descending from the gravimeter, measure the center of gravity sway for 30 s in the same manner as above when a current of 100, 200, 300, 500, 700, 1,000, 1,200, 1,500, 1,700, or 2,000 μA is applied.

The optimal intensity is the current intensity that improves the total trajectory length the most among several consecutive current intensities that improve the total trajectory length below the sensory threshold in six stimulus intensities from 100 µA to 1,000 µA. When the subject complains of the interruption, the optimal intensity is determined from the stimuli that have been performed up to that point. The current intensity is increased up to a maximum of 2,000 μA to determine whether or not pain is felt. However, the test is terminated when the subject feels pain. The minimum current intensity at which the subject feels a stimulus specific to the noisy GVS is used as the sensory threshold.

The adverse events before, during, and after the stimulation for consideration of optimal stimulation, and failure checks during stimulation are noted.

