### Safety analysis Methods

　The safety analysis set will be used for the safety analysis. During the analysis of safety data, tabulations and lists of data will be prepared and no statistical tests will be performed.

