#### Adverse events

　Adverse events will be coded according to the ICH International Pharmacovigilance Dictionary (MedDRA), classified by organ category (SOC) and basic term (PT), and tabulated by stimulus.

　A separate list of deaths, serious adverse events, or adverse events resulting in discontinuation and other significant adverse events will be prepared.

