### Data management

Data quality control is conducted by monitoring and data management in accordance with the standard operating procedures established prior to the clinical trial by the coordinating investigator conducting the clinical trial.

Data management will identify and implement the most effective data collection and management methods for the study protocol and present data sets that meet the objectives of the study protocol.

The subject data will be entered into an electronic Case Report Form designated by the investigator and sent electronically to the coordinating investigator, and will be matched with other data in a validated data management system.

Data management is performed in accordance with applicable data cleaning procedures and is intended to ensure data integrity, including the removal of data errors and inconsistencies. Adverse event terms and concomitant drug names are coded using the latest version of MedDRA (ICH International Glossary of Pharmaceutical Terms) and the drug name data file, respectively.

The electronic Case Report Forms (including queries and audit trails) will be retained by the coordinating investigator and a copy will be sent to the investigator and retained as the investigator's copy. In no event will subject initials be collected and reported to the coordinating investigator.

In addition, the case report forms will not be prepared for subjects who did not use the investigational device, such as subjects deemed ineligible to participate in the clinical trial.

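### The safety set is drawn from enrolled patients, which on the protocol's predominant usage leaves out about 9 to 10 of 60 planned subjects who were stimulated in the intensity test but had no optimal intensity

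*Protocol*

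**What the plan says.** Section 12.2.2 defines the safety analysis set: "Of the enrolled patients, the SAS shall consist of those patients in whom at least one safety endpoint was evaluated". Section 12.2.5 gives it sole use: "The safety analysis set will be used for the safety analysis". No other set or tabulation is named for subjects who were stimulated but went no further.

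Enrolment has two steps (Section 10.2). Eligible, consenting subjects are provisionally enrolled and take the intensity test. Full enrolment follows only if the test succeeds: "Only subjects with optimal intensity will be enrolled in the study". Under Section 11.3.3, success means at least a 10% shortening of total trajectory length at the best current, within a run of consecutive improving currents below the sensory threshold.

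The test uses the device itself. Sway is measured for 30 s at each of ten stepped currents. On the range, Section 11.3.3 says: "The current intensity is increased up to a maximum of" 2,000 μA, with the test ending if pain is felt.

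Subjects without an optimal intensity are stopped there, and their safety is confirmed 2 weeks later (Sections 6.1.2 and 11.3.3). Adverse events are collected from consent onward (Section 11.6.2) and are checked before, during and after the test stimulation (Sections 11.3 and 11.3.3).

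**The concern.** A safety set normally contains everyone exposed to the product. Here exposure begins with the intensity test, but membership of the set appears to begin with full enrolment, which comes after the test and depends on its result. Subjects whose sway did not improve enough would then count in the denominator of no safety table, even though they were stimulated, watched and followed up.

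Two things are at stake. The adverse event rate would be estimated only in subjects selected for a favourable response to the device. In addition, the same definition gives a planned denominator of 50 or 60 depending on how one word is read, and that should not be open when the data are tabulated. Section 11.6.5 anticipates pain, dizziness, nausea, headache, falls and skin reactions, and none of these is confined to subjects who have an optimal intensity.

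**Working it through.** **1. What *enrolled* means, place by place.**

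| Place | Usage |
|---|---|
| Section 10.2, full enrollment | Only subjects with an optimal intensity |
| Section 11.1, schedule footnote 5 | Same |
| Section 11.3 and end of 11.3.3 | Same |
| Section 12.1.1 | "The target number of patients for this clinical trial will be set at 60 (50 enrolled in the main study and 40 completed" |
| Section 12.1.2 | "The target number of patients is set to 60 (50 enrolled and 40 complete" |
| Section 10.2, opening sentence | All consenting, eligible subjects |
| Section 8.1.5 | Device used only in enrolled subjects, which would have to include those in the intensity test |

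Five places give the narrow meaning, two of them in Section 12, where the safety set is defined. Two places give the wide one.

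**2. Reproducing the plan's own numbers.** Inputs from Section 12.1.2: 40 completers, 20% dropout, 15% without an optimal intensity. Formula: N / (1 − loss).

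- Full enrolment: 40 / (1 − 0.20) = 50, as stated.
- Provisional enrolment: 50 / (1 − 0.15) = 58.8, rounded up to 59. The protocol states 60, which is close enough to be rounding.

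So the step from 60 to 50 is the loss at the intensity test.

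**3. Subjects stimulated but outside the set on the narrow reading.**

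- By the targets: 60 − 50 = 10, and 10 / 60 = 16.7%.
- By the stated rate: 60 × 0.15 = 9, or 15%.

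**4. What the difference in denominator does.** With no events observed, the one-sided 95% upper bound on an event rate is 1 − 0.05^(1/n).

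- n = 50: 5.8%.
- n = 60: 4.9%.

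The chance that 10 omitted subjects include at least one event with true rate p is 1 − (1 − p)^10. It is 9.6% at p = 1%, 18.3% at p = 2% and 40.1% at p = 5%. The rates p are illustrative; the protocol gives none.

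**5. Is the information there?** Collection runs from consent, and the 2-week check is specified. Section 13.4.2 says "case report forms will not be prepared for subjects who did not use the investigational device". By the converse, stimulated subjects should have forms, though this is an inference and is not stated. The gap is in the analysis set, not in data collection.

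**The case against.** The best reply is that exclusion is one reading only. The opening of Section 10.2 enrols every eligible subject and treats provisional and full enrolment as two stages. Section 8.1.5 would forbid the intensity test itself unless those subjects counted as enrolled. The full analysis set requires a visit in Session I or II, whereas the safety set requires only one safety evaluation. There are also safeguards: Section 10.1 documents completion or discontinuation for subjects who were tested, and Section 12.2.2 requires exclusions and their reasons to be given in the study report. This stands in part. The wide reading is possible, so the omission is not certain. But the wording supports the narrow reading more often, including in the same section, and a definition that yields either 50 or 60 still needs correcting.

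A reader might infer four stronger things that the documents do not support.

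- *The highest currents are missing from the safety analysis.* They are not. The 50 fully enrolled subjects take the same test, and their events from it stay in the set.
- *The test is the highest exposure in the trial.* It has the highest current but not the highest exposure. The ten currents sum to 9,200 μA; at about 30 s each that is 276,000 μA·s. Four hours at the lowest step, 100 μA, is 100 × 14,400 s = 1,440,000 μA·s, about five times as much. Not every subject reaches 2,000 μA.
- *Stopping for pain drives exclusion, so the omitted group carries more events.* Only currents below the sensory threshold and no higher than 1,000 μA can be optimal. Pain generally arises at currents that are felt and so are already ineligible. After an interruption, the optimum is still taken from the steps completed. A very early stop could leave fewer candidates, but nothing shows how often.
- *The adverse event table has no place for test-phase events.* Section 12.2.5 says only that events are classified "and tabulated by stimulus". That does not exclude such a column, and Section 12 leaves tabulation details to the statistical plan.

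**Conclusion.** The concern holds in a limited form. On the predominant meaning of *enrolled*, the protocol fixes a safety set that leaves out about 9 to 10 of 60 planned subjects (15–17%) who received device current, and that is conditioned on response to the device. On the wider meaning nobody is left out, and the defect is an ambiguous definition.

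The count is a planning figure. It assumes that all 60 subjects reach the intensity test and that failures occur at the stated rate. Whether the omitted subjects have more or fewer events than the rest cannot be told from the document, so no direction of bias is claimed. Efficacy conclusions are untouched. Because the rule is stated in the protocol and not merely left open, a statistical plan that follows it would inherit the problem.

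**What to change.** In Section 12.2.2, define the safety analysis set as every subject who received any stimulation from the investigational device, including provisionally enrolled subjects in the intensity test. Use *provisionally enrolled* and *fully enrolled* throughout, and align Section 8.1.5 and the opening of Section 10.2 with that wording.

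In Section 12.2.5, state that adverse events and device defects from the intensity test are reported separately from those in the GVS and placebo sessions, with the number stimulated in each as the denominator. The exact table layout can stay with the statistical plan.

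The cost is one reworded definition and one added line on reporting. No new assessments are needed, provided that case report forms exist for subjects stopped after the test, which should be confirmed. Sample size and efficacy analyses do not change. The change should be made before the allocation key is opened.
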